## Abstract

**Background:**

Patients who require intensive care unit (ICU) care frequently develop hospital-acquired functional decline, defined as a new or worsening loss of ability to perform self-care activities that is associated with prolonged immobility. This morbidity may persist for months to years after hospitalization but is potentially preventable through initiating mobility in the ICU using a multidisciplinary, evidence-based intervention to maintain functional status. While guidelines for ICU physical activity exist, timely identification of patients suitable for activity interventions is an ongoing challenge due to the dynamic nature of critical illness and the number of locations in the electronic health record (EHR) that clinicians need to click in and out of to synthesize patient data. Therefore, there is a critical need to develop an effective knowledge-based clinical decision support system (CDSS) interface in the EHR for efficient identification of patients appropriate for physical activity interventions and coordination of patient-specific activity plans within the ICU team.

**Objective:**

The objective of this 2-phase project is to develop a CDSS interface for consistent translation of patient-specific data to inform evidence-based physical activity interventions delivered by registered nurses and physical therapists in ICU settings and evaluate its usability, usefulness, cognitive workload, acceptability, feasibility, and effectiveness on decision-making outcomes.

**Methods:**

In phase 1, we will develop a usable, useful, and acceptable CDSS prototype by conducting 4 rounds of user-centered design interviews with registered nurses and physical therapists by using think-aloud and cognitive interview methods. In preparation for implementing CDSS in phase 2, we will conduct semistructured stakeholder interviews using the Consolidated Framework for Implementation Research to identify clinical workflow considerations, potential barriers, and implementation strategies. In phase 2, we will evaluate CDSS’s usability, cognitive workload, acceptability, and effectiveness for activity guideline adoption in two settings: (1) a simulated EHR environment and (2) two adult ICU units in a tertiary care hospital.

**Results:**

This study received funding in April 2024. The CDSS development phase is expected to conclude by December 2025. Data collection and analysis of CDSS evaluation are expected to begin in April 2026 and conclude by December 2028.

**Conclusions:**

We expect the results of this multimethod process for designing, testing efficacy, and identifying barriers to real-world use to have an important positive impact on others who seek to develop safe and effective CDSSs that align with clinical workflow. Importantly, this work will complete the necessary pilot study for a subsequent multisite pragmatic clinical trial to scale the concurrent use of patient data with guideline recommendations at the point of care to deliver evidence-based interventions to reduce hospital-acquired functional decline and its negative, costly outcomes.

**International Registered Report Identifier (IRRID):**

DERR1-10.2196/75752

## Introduction

### Background

New functional impairment after hospitalization for critical illness is common and persistent. More than 5 million adults are admitted to intensive care units (ICUs) each year in the United States, and more than 50% of them develop new physical health problems or hospital-acquired functional decline [1-4]. Functional decline is associated with negative outcomes during and after hospitalization, including ICU readmission, prolonged hospitalization, hospital readmission, nursing home admission, inability to return to work, and death [5-8]. These significant and long-term patient consequences demonstrate an urgent need to mitigate hospital-acquired functional decline.

The etiology of functional decline includes a combination of preexisting health status, the acute illness, and the consequences of ICU care (eg, deep sedation, immobility) [9,10]. The results of rigorous, well-designed studies demonstrate that early and routine physical activity interventions are safe and effective in improving functional recovery by the time of hospital discharge [11-13]. Multiple clinical practice guidelines recommend physical activity interventions as part of a bundle of standardized care for all patients in the ICU [14,15]. The ABCDEF bundle (Figure 1) was developed to standardize processes for coordinating and delivering evidence-based interventions in the ICU [16,17]. The early mobility (“E”) bundle element describes daily, progressive physical activity interventions for physiologically stable patients, beginning with exercises in bed, transferring to a chair, and advancing to walking. The results of ABCDEF bundle implementation studies demonstrate the benefits of increased frequency and level of physical activity, decreased ICU and hospital lengths of stay, and decreased mortality [18-20]. However, reliable implementation of all elements remains challenging. A national, 68-hospital quality improvement collaborative study routinely measured ABCDEF bundle implementation performance and found that mobility was the least frequently implemented bundle element, with only 29% of patients receiving physical activity interventions beyond active range of motion [20]. To improve overall ABCDEF bundle implementation and patient outcomes, specific focus on innovative strategies to overcome barriers to physical activity is needed.

**Figure 1 figure1:**
[figure not shown]
The ABCDEF bundle of standardized care. SAT: spontaneous awakening trial; SBT: spontaneous breathing trial.

Numerous barriers to physical activity interventions have been identified and broadly classified as patient-, clinician-, unit-, protocol-, or ICU context–related barriers [21]. Strategies to address these barriers have included the use of structured quality improvement models to identify and target local barriers [22], nursing-initiated physical activity protocols to standardize patient assessment and goal setting [23], and focused interdisciplinary communication and collaboration [24,25]. However, these resources and approaches have not spread widely. A limitation to physical activity protocols is the poor usability, given the temporal and cognitive demands associated with the workflows of registered nurses (RNs). Our previous research identified that obstacles to existing RN-initiated physical activity protocols are significant—requiring time to synthesize multiple patient data elements either across different locations in the electronic health record (EHR; eg, blood pressure in vital signs documentation and vasopressor dose in the medication administration record) or scrolling through data over several hours or shifts to determine patient stability or changes in condition (eg, determining whether current ventilator settings represent an increased, decreased, or unchanged amount of respiratory support) [26].

Clinical decision support system (CDSS) interventions are particularly relevant in ICU settings to support decision-making and reduce cognitive load stemming from the large amounts of data from disparate areas of the EHR that clinicians must filter and process to make time-critical decisions [27,28]. CDSSs can provide data visualizations, alerts, reminders, dashboards, and decision support to augment clinicians in complex decision-making and support coordinated care delivery [29,30]. CDSSs can play an important role in the timeliness of physical activity decision-making, which significantly impacts patient outcomes. There is significant evidence that bed rest duration is associated with loss of muscle mass and strength and subsequent functional decline, which begins within 24 hours of bed rest and rapidly worsens, with a loss of up to 5% to 10% of muscle strength within 7 days of bed rest [31,32]. Nevertheless, there remains a lack of multidisciplinary EHR-integrated CDSSs designed to enhance critical thinking, promote guideline adoption, and decrease the cognitive burden of this complex decision-making process. In addition, compared to medical CDSSs, few CDSSs have been designed and tested for ICU RNs and even fewer for physical therapists (PTs) [33]. Given that physical activity interventions are delivered by multiple ICU team members, a CDSS is needed to support decision-making and physical activity care coordination across disciplines within the ICU team. Considering the low implementation of physical activity interventions during hospitalization, especially in ICU settings, it is imperative to identify methods to increase the adoption of evidence-based physical activity interventions.

### Study Objectives

The overall objective of this 2-phase project is to develop and evaluate a CDSS interface for consistent translation of patient-specific data to inform evidence-based physical activity interventions delivered by RNs and PTs in ICU settings. Our team has successfully developed and validated a knowledge-based algorithm to synthesize patient data from multiple areas of the EHR with physical activity guideline recommendations (Aggregating Patient Safety and Status Information to Support Time-Sensitive Interventions in the Intensive Care Unit [ASSIST-ICU]) [34]. In phase 1, we aim to (1) develop the ASSIST-ICU CDSS interface using user-centered design (UCD) interviews with RNs and PTs and (2) develop a plan for implementing CDSS in 1 health system by interviewing key stakeholders. In phase 2, we aim to evaluate the effectiveness of the ASSIST-ICU CDSS for increasing the use of evidence-based physical activity interventions in the ICU delivered by RNs and PTs in (1) a simulated EHR environment and (2) a real-world pragmatic trial. The phase 2 secondary objectives are to evaluate the usability, usefulness, cognitive workload, acceptability, and implementation feasibility of the ASSIST-ICU CDSS.

### ASSIST-ICU Algorithm Development

ASSIST-ICU is a knowledge-based algorithm using discrete nursing, respiratory therapy, and physical therapy documentation to synthesize patient data with physical activity guideline recommendations. The ASSIST-ICU algorithm was developed using an iterative process involving (1) translating expert recommendations into operational definitions, (2) identifying discrete data fields in the EHR, and (3) developing logic statements for the algorithm [35]. We used an expert consensus statement on early mobility readiness and safety criteria to develop operational definitions in 4 domains: respiratory, cardiovascular, neurological, and other [36]. An example from the respiratory domain is shown in Table 1. Each domain is evaluated using 24 hours of data to score a patient’s readiness for mobility (yes or no). Overall readiness is scored as “yes” only if all domains are scored as ready for mobility; if any domain is scored as “no,” the overall readiness score is “no.”

Our team established content validation of the operational definitions [37], and retrospective testing of the decision support rules has been published [34]. The ASSIST-ICU CDSS will be delivered via an EHR tool. Initial feedback from focus groups will inform prototype development to include an icon that indicates readiness for mobility (“yes” or “no”) with the ability to drill down to the features contributing to the score, providing details on why the patient met or did not meet the readiness elements.

**Table 1 table1:** Example of algorithm development process from the respiratory domain.

Variables	Description
Expert recommendation [36]	Clinical considerations for maintaining respiratory safety with out-of-bed exercises include that an artificial airway (eg, endotracheal tube, tracheostomy tube) is not in itself a contraindication, and SpO_2_^a^ should be ≥90%
Operational definition	If a patient is receiving mechanical ventilation, the patient’s most recent SpO_2_ reading and the 24-hour average SpO_2_ reading must be ≥90%
Data fields	Medical device group=endotracheal tube or tracheostomy SpO_2_ row
Logic statement	If medical device group=endotracheal tube OR tracheostomy tube, then most recent SpO_2_ reading ≥90% AND 24-hour average SpO_2_ reading ≥90%

^a^SpO_2_: peripheral capillary oxygen saturation.

### Conceptual Framework

The theoretical basis for our study is grounded in an understanding of technology acceptance, cognitive load theory, and implementation science (Figure 2).

**Figure 2 figure2:**
[figure not shown]
The 4 components of the study. ASSIST-ICU: Aggregating Patient Safety and Status Information to Support Time-Sensitive Interventions in the Intensive Care Unit; CDSS: clinical decision support system.

The technology acceptance model (TAM) is a widely used evidence-based model that focuses on perceived ease of use (or usability) and perceived usefulness. More than 30 years of research show that the TAM explains a substantial portion of health information technology acceptance and use [38,39]. Although multiple modifications of the TAM exist, we use the original TAM model for its parsimony, ease of use, and usefulness in explaining acceptance [40]. Cognitive load theory, a theory in use for more than 30 years, focuses on complex problem-solving when excessive cognitive load decreases decision-making performance [41,42]. A suboptimal CDSS design would increase extraneous cognitive workload and decrease a user’s ability to correctly interpret the evidence presented. Given the limited amount of information humans can process in working memory before experiencing cognitive overload, our CDSS will aim to minimize extraneous cognitive load and will be evaluated using the NASA Task Load Index (NASA-TLX) [43]. Technology use is also influenced by organizational factors that are addressed by implementation science. The Consolidated Framework for Implementation Research (CFIR) organizes 39 constructs across 5 domains: innovation, outer setting, inner setting, individual characteristics, and implementation process [44,45]. This study will focus primarily on the CFIR domains of inner setting (organization and unit), characteristics of individuals (clinicians), and implementation process.

## Methods

We will use a 2-phase approach using UCD and implementation science methodologies to develop a CDSS tool, implement the tool in 1 health system, and then test the tool in 2 settings (Figure 3).

**Figure 3 figure3:**
[figure not shown]
Details of the study’s 2 phases. CDSS: clinical decision support system; EHR: electronic health record; ICU: intensive care unit.

### Phase 1: ASSIST-ICU CDSS Prototype Development and Implementation Plan

#### Iterative UCD Cycles to Design the ASSIST-ICU Prototype

We will design and iteratively revise the ASSIST-ICU CDSS prototype in a series of 4 UCD cycles with practicing critical care clinicians per cycle (n=24 RNs and PTs). We will conduct 2 types of sequential interviews—think-aloud [46] and cognitive [47] interviews—as well as a survey to assess acceptability (Multimedia Appendix 1) [38]. In the think-aloud interviews, participants will receive information about 2 patients with differing physical activity needs and will be instructed to open the prototype and navigate through the interface as they would if they were gathering clinical information in the EHR for making a clinical physical activity decision. As they explore the interface, they are instructed to vocalize about the actions they are taking and the thought processes they are using to interact with the prototype. This is a well-accepted usability method in which the clinician is not interrupted during their exploration. This method elicits users’ expectations, understanding, and misunderstanding and identifies usability problems [48]. To capture interpretations and features that may have been missed during the think-aloud interview, a cognitive interview will be conducted to assess clinician understanding and interpretation of the prototype features. In this method, we systematically review the prototype interface with the clinician, feature by feature, to assess whether the feature was interpreted as the designers intended as well as to solicit design ideas. Next, to assess acceptability, the participant will complete the TAM survey (Cronbach α=0.79-0.93) [49].

The design team will analyze the findings of the interviews by rating each feature as being positive, negative, or unclear using the following deductive coding categories: (1) ease of use, (2) usefulness, (3) interpretation, and (4) satisfaction. Features with ≥25% negative or unclear ratings will be redesigned [50]. Any redesign efforts will incorporate EHR feasibility into the methods to avoid unattainable solutions. After redesign, clinician interviews will resume with a new group of participants.

#### ASSIST-ICU CDSS EHR Integration

After completing the UCD process, we will collaborate with the clinical informatics team at our study site to build the final prototype of the ASSIST-ICU CDSS interface in their EHR training environment. To support simulated testing, we will create real-world simulated patients with simulated data to evaluate how the data will be displayed on the screen and how clinicians can interact with the data. Our CDSS design will aim to include primarily structured data fields that are already available in the EHR to minimize creating custom documentation fields to keep the design within a Fast Healthcare Interoperability Resources infrastructure that will allow for future interoperability between sites.

#### ASSIST-ICU CDSS Implementation Plan

We will gather input from key stakeholders to identify clinical workflow considerations, potential barriers, and implementation strategies for the ASSIST-ICU CDSS using a descriptive qualitative design, incorporating the CFIR to inform data collection and directed content analysis [44,45]. We will interview stakeholders using a semistructured interview guide (Multimedia Appendix 2). Interview questions will focus on (1) workflow considerations, (2) role needs, and (3) implementation strategies to prepare our team and participating site for the successful evaluation of CDSS. Questions will be tailored to key stakeholders (eg, ICU director of nursing, PT director, RN informaticist, and chief medical information officer), recognizing that individuals hold different levels of influence within the organization. Interview data will be analyzed using directed content analysis [26,51]. We will review findings from the interviews to identify a follow-up plan for overcoming potential barriers and addressing workflow considerations before the ASSIST-ICU CDSS clinical trial.

### Phase 2: ASSIST-ICU Simulated Trial Design

#### Overview

We will conduct a simulated trial comparing the ASSIST-ICU CDSS interface with usual care (no ASSIST-ICU interface) in a simulated EHR environment. We will operationalize evidence-based decision-making through the creation of 6 expert-validated clinical scenarios. Of the 6 simulations, 3 will meet the out-of-bed safety definition, and 3 will not. All 6 simulations will be completed by each participant in a random order generated using the RAND function of Microsoft Excel. The decisions (regarding whether out-of-bed activity is safe or unsafe) will be recorded, and the number of correct decisions (range 0-6) for each participant will serve as our outcome measure of effectiveness (Table 2).

**Table 2 table2:** Operationalization for scoring each clinical scenario.

	ASSIST-ICU^a^ CDSS^b^ recommends patient out of bed: yes	ASSIST-ICU CDSS recommends patient out of bed: no
Clinician decision to mobilize patient out of bed: yes	1	0
Clinician decision to mobilize patient out of bed: no	0	1

^a^ASSIST-ICU: Aggregating Patient Safety and Status Information to Support Time-Sensitive Interventions in the Intensive Care Unit.

^b^CDSS: clinical decision support system.

#### Study Participants for Simulated Trial

The inclusion criteria will be as follows: (1) licensed RN or PT, (2) at least 6 months of experience working in an ICU (to align with the advanced beginner stage of the Dreyfus model of skill acquisition [52,53]), (3) access to a tablet or computer for the design session, and (4) fluent in English. The exclusion criteria will be as follows: (1) no EHR experience in a critical care setting and (2) inability to use a cloud-based video platform.

We will recruit a sample of 50 licensed RNs and PTs (control group: n=25, 50%; intervention group: n=25, 50%) using publicly available lists from the professional state boards of 7 geographically diverse states. We will randomly select clinicians to contact. Using a modified version of the tailored design method proposed by Dillman et al [54], each selected clinician will be contacted using different modes (ie, letters, postcards, and email) up to 5 times in a 21-day cycle. For generalizability purposes, we will use a quota sampling methodology to ensure that the clinicians represent the demographics of the profession [50]. In addition to the random sample, up to 15 clinicians will be recruited using convenience sampling to assess the fidelity of ASSIST-ICU (eg, agreement between clinical scenario sequence and variable display in CDSS) in the simulated EHR.

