#### Sample Power for Simulated Trial

The primary hypothesis to be tested in this study focuses on the efficacy of ASSIST-ICU in making evidence-based guideline physical activity decisions in a simulated EHR environment compared to no decision support. We hypothesize that participants assigned to the ASSIST-ICU intervention group will achieve a higher proportion of decisions that meet the out-of-bed safety definition. Assuming a true mean of 4.5 correct decisions out of 6 simulations (75% probability) when using the decision tool and 3 correct decisions (50% probability) when not using it, 2-sample binomial test simulations show that 25 clinicians per group will provide 99.2% power when testing for a between-group difference at α=.05.

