#### Study Procedures and Setting

Respondents who meet the eligibility criteria will participate in an informed consent process and complete a short demographic and clinical experience survey. At the time of the scheduled test session, participants will connect via the cloud-based video platform from their homes or a quiet space of their choosing. Each participant will connect with a member of the research team and share their screen as they interact with the prototype. This will allow the visualization of computer mouse movements to show which areas and features of the prototype they are focusing on. After receiving a standardized orientation to the simulated EHR environment, the research team member will begin recording, and the clinicians will open the simulated EHR environment (with or without the ASSIST-ICU CDSS) to begin the study. The fictional patients’ scenarios will be presented in their preassigned random order. After exploring the EHR environment, participants will be asked to respond whether they (1) would or (2) would not decide to move each patient out of bed that day.

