#### Data Collection and Analysis for Simulated Trial

Clinicians will receive a score ranging from 0 to 6 based on the number of scenarios answered correctly. Participants will complete 3 brief surveys using a hyperlink in the cloud-based video platform’s chat feature to assess the usability (System Usability Scale [SUS] [55]), cognitive workload (NASA-TLX [43]), and acceptability (Acceptability of Intervention Measure [AIM] [56]) of CDSS and decision-making process as a whole. The SUS is a 10-item Likert-type scale that is widely used to measure usability across a broad range of interfaces and performs well psychometrically (Cronbach α=0.70-0.92) [57,58]. The NASA-TLX is a 6-item scale that measures subjective cognitive workload in performing a specific task and is a reliable measure of cognitive workload across industries, including ICU clinicians (Cronbach α=0.83-0.92) [59]. The AIM is a 4-item Likert-type scale that measures acceptability and performs well psychometrically (Cronbach α=0.85-0.91).

Summary statistics will be calculated for the collected measures by group. Continuous measure distributions will be assessed for normality and reported as means and SDs or medians and IQRs, as appropriate. Categorical measures will be reported as counts and percentages for each level. A 2-sample binomial test will be used to test the null hypothesis that decision accuracy with the support tool does not differ from accuracy without it. Further between-group assessments will be conducted for SUS, NASA-TLX, and AIM scores using 2-sample 2-tailed *t* tests or the Wilcoxon rank sum test. *P* values will be reported based on 2-sided alternatives, and statistical significance will be evaluated at α=.05.

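### Simulated trial: the stated primary test pools nurses' and therapists' decisions without adjusting for profession, so any accuracy gap between them is unmodelled variation between clinicians

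*Protocol article*

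**What the plan says.** All statements are in the protocol article, in the sections on the phase 2 simulated trial.

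- **Sample** (Study Participants for Simulated Trial): "We will recruit a sample of 50 licensed RNs and PTs", 25 per group. No RN:PT split is given. Being an RN or a PT is an eligibility criterion, so profession is known before anyone is assigned.
- **Baseline data** (Study Procedures and Setting): before the session participants "complete a short demographic and clinical experience survey".
- **Outcome** (Overview): "All 6 simulations will be completed by each participant in a random order generated using the RAND function of Microsoft Excel". Each clinician's number of correct decisions, 0 to 6, is the effectiveness measure.
- **Power** (Sample Power for Simulated Trial): the control rate is taken as 50%, or 3 of 6, and the rate with the tool as 75%, or 4.5 of 6. On that basis "25 clinicians per group will provide 99.2% power when testing for a between-group difference at α=.05".
- **Primary test** (Data Collection and Analysis for Simulated Trial): "A 2-sample binomial test will be used to test the null hypothesis that decision accuracy" is the same with and without the tool, two-sided. No covariate or stratum is named.
- **Assignment to arms**: no method is described. The article details random scenario order and random selection of clinicians to contact. Random assignment is only implied, by a remark on randomized tests of efficacy in Study Significance and Strengths.

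**The concern.** A 2-sample binomial test has no place for profession, and it takes the six decisions of one clinician to be as independent as decisions from six clinicians. If RNs and PTs differ in how often they judge out-of-bed safety correctly, two decisions by the same clinician are alike partly because they come from the same profession. The test's standard error leaves this out.

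Two things are at stake. The first is the type I error of the primary comparison, which rises above 5% when assignment is not stratified. The second is precision: variation between professions stays in the error term although a known covariate could remove it. The article gives no RN-PT accuracy gap, so every size below rests on an assumed gap.

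**Working it through.** **1. The plan's own figure.** Inputs: 25 clinicians per arm, 6 decisions each, 50% v 75%, two-sided α = 0.05 (Overview, Study Participants, Sample Power and Data Collection sections). With 25 × 6 = 150 independent decisions per arm, power is 99.5% by the pooled z test and 99.3% by Fisher's exact test or the continuity-corrected z test. A t test on the 0-6 scores, with independent decisions, gives 99.4%. The stated 99.2% is reproduced. One binary outcome per clinician (25 per arm) would give 44.5%. So the stated power rests on independence of the six decisions.

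**2. Chance imbalance if allocation is a simple 25/25 split** (an assumption, as is the number of PTs). By the hypergeometric distribution, the arms differ by 5 or more PTs in 21.7% of allocations with 15 PTs of 50, and in 25.8% with 25 PTs. A 5-PT difference is 5/25 = 20 points of PT share. With an assumed 20-point accuracy gap it moves the arm difference by 0.20 × 0.20 = 4 percentage points.

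**3. Type I error of the stated test.** Assume 60% correct in both arms, accuracy gap g and PT share s.
- Variance between clinicians due to profession = g² s(1 − s).
- Equivalent ICC ρ = g² s(1 − s) / (0.6 × 0.4).
- Design effect = 1 + 5ρ.
- Type I error = 2[1 − Φ(1.96/√design effect)].

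| Gap | PTs of 50 | ρ | Design effect | Type I error, formula | Type I error, simulation |
|---|---|---|---|---|---|
| 0 | 15 or 25 | 0 | 1.00 | 5.0% | 5.1% |
| 10 points | 15 | 0.0021/0.24 = 0.009 | 1.04 | 5.5% | 5.9% |
| 10 points | 25 | 0.0025/0.24 = 0.010 | 1.05 | 5.6% | 5.6% |
| 20 points | 15 | 0.0084/0.24 = 0.035 | 1.18 | 7.1% | 7.0% |
| 20 points | 25 | 0.0100/0.24 = 0.042 | 1.21 | 7.5% | 7.6% |

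The simulations used 20,000 runs per setting; a separate set gave up to 8.2% at 20 points with 25 PTs. At an assumed 30-point gap, with 10 or 24 PTs, the simulated error is 9% to 12%.

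**4. Adding other variation between clinicians**, with an assumed ICC of 0.1 within profession:
- No profession gap: design effect 1 + 5 × 0.1 = 1.5, type I error 11.0% (simulation 11% to 12%).
- 20-point gap, 15 PTs: ρ = (0.1 × 0.2316 + 0.0084)/0.24 = 0.13, type I error 12.8%.
- 20-point gap, 25 PTs: ρ = (0.1 × 0.23 + 0.01)/0.24 = 0.14, type I error 13.1%.
- Simulation for the last two gives 13% to 14%.

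So clustering alone takes the error from 5% to about 11%, and the profession gap adds about 2 points more.

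**5. The alternative.** A linear model of the 0-6 score on arm and profession had a simulated type I error between 4.8% and 5.5% in every setting of steps 3 and 4 with unstratified allocation.

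**6. Power of a clinician-level analysis without and with profession** (simulation, ICC 0.1, 15 or 25 PTs):

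| True accuracy | Gap | Without profession | With profession |
|---|---|---|---|
| 50% v 75% (planned) | 0 | 95% | 95% |
| 50% v 75% (planned) | 10 points | 95% | 95% |
| 50% v 75% (planned) | 20 points | 93% | 96% |
| 60% v 75% (assumed) | 20 points | 55% to 57% | 60% to 63% |

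Without the extra clustering, the stated test keeps at least 98% power at the planned effect for every gap from 0 to 30 points.

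**The case against.** The strongest reply is that the article contradicts nothing here, and that an article commonly leaves stratification factors and adjusted models to the full protocol or analysis plan. For the method of assignment this stands. A reader might infer that no balancing by profession is planned, but the article is silent on assignment, and silence does not establish that. The reply does not reach the test itself: the article names an unadjusted test and powers the trial on it.

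Three other stronger readings also fail.

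- **Quota sampling.** A reader might take the quotas as fixing an RN:PT mix. The text ties them to the demographics of the profession, for generalizability. It sets no split between RNs and PTs and does not concern balance between arms.
- **Bias.** A reader might infer that the result could simply reflect who was in each arm. Under random assignment, chance imbalance is noise, not bias. The 4-point shift in step 2 compares with a planned difference of 25 points and a standard error of about 6 to 7 points.
- **Lost power.** A reader might infer that ignoring profession leaves the trial short of power. At the planned effect it does not. The gain of 5 to 7 points from the covariate appears only at a smaller effect such as 60% v 75%.

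It is also fair to say that the larger validity problem is clustering of six decisions within a clinician, and that the clinician-level analysis, not the covariate, cures it. That stands, and the covariate should not be credited with it.

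**Conclusion.** The point holds as a minor improvement to a stated analysis. The primary test pools RN and PT decisions and cannot use profession, which is known at entry. If allocation is unstratified, an assumed RN-PT gap of 20 points takes its type I error to about 7% to 8%; a 10-point gap takes it to about 6%, and no gap leaves it at 5%. With an assumed ICC of 0.1 as well, it is about 13%, most of the excess being due to clustering. A clinician-level model with profession holds about 5%. At the planned effect the covariate adds 0 to about 3 points of power.

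These sizes depend on the accuracy gap, the RN:PT mix, the ICC, the 60% accuracy used under the null and simple 25/25 allocation. The article gives none of these. If assignment is already stratified by profession, the part of the error due to profession disappears (simulated error 4.0% to 5.6% without other clustering), but the part due to clustering remains.

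**What to change.** Replace the 2-sample binomial test as the primary comparison with a clinician-level analysis of the 0-6 score, such as a linear model with arm and profession, profession being a prespecified covariate. State the method of assigning clinicians to arms and the RN:PT target. If not already planned, assign 1:1 within RN and PT strata.

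Stratification and adjustment belong together. With stratified assignment, an unadjusted t test on the scores becomes conservative: simulated type I error was about 3% at a 20-point gap with no other clustering.

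The cost is one model term (one degree of freedom) and a second allocation list. No extra participants or data are needed.
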